## 7 Risks of Intervention

The primary focus of our study is to determine if a VTE risk prediction tool increases the number of high-risk patients reviewed by the pediatric VTE research team. The majority of the patients in the study will be considered low risk (based on previous data, we anticipate >90% of all patients to fall into this category). High-risk patients in the intervention arm will receive an additional chart review and subspecialty expertise. Part of that subspecialty expertise may include recommendations to initiate prophylactic anticoagulation. The use of pharmacologic anticoagulation is the standard of care among peer pediatric institutions and among adult hospitalized patients (including at Vanderbilt University Medical Center). In fact, nearly all adult patients are provided some type of VTE prophylaxis upon admission. The decision to start patients on prophylactic anticoagulation is complex and involves consideration of the patient's clinical status and review for possible contraindications. We would not consider patients for anticoagulation with severe bleeding disorders, clinically significant hemorrhage, severe renal dysfunction, or anything in the opinion of the investigator that would jeopardize the safety of the subject. Pharmacologic prophylaxis is performed using various anticoagulant medications, most commonly with heparin or enoxaparin.

These drugs are commonly used, FDA-approved for anticoagulation, and considered to be safe; side effects of these medications include injection site reactions, bleeding, and rarely, thrombocytopenia. In several studies of pediatric VTE pharmacologic prophylaxis, there were very few bleeding episodes reported.

## 8 Reporting of Adverse Events or Unanticipated Problems Involving Risk to Participants or Others

### 8.1 Definition of Adverse Event

An Adverse Event (AE) means any untoward medical occurrence associated with the use of an intervention in humans, whether or not considered intervention related. An AE can therefore be any unfavorable and unintended sign (including an abnormal laboratory finding), symptom, or disease temporally associated with the use of a medicinal (investigational) product. Any medical condition present at the time of enrollment will be considered as baseline and not reported as an AE.

| Table 1            |                                                                            |
|---------------------------|----------------------------------------------------------------------------|
| WHO bleeding scale |                                                                            |
| Grade 0                   | No bleeding                                                                |
| Grade 1                   | Petechial bleed                                                            |
| Grade 2                   | Mild blood loss (clinically significant)                                   |
| Grade 3                   | Gross blood loss requires transfusion (severe)                             |
| Grade 4                   | Debilitating blood loss, retinal/cerebral bleed (associated with fatality) |

Due to the nature of the study, which is being performed to evaluate a clinical support tool, we anticipate minimal AEs. Due to the possible clinical recommendation for anticoagulation, we are planning to only collect coagulation/hemostasis-related AE's in the study. We will use the WHO bleeding scale to grade any bleeding events (table 1).

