### 8.2 Definition of Serious Adverse Event

An AE or suspected adverse reaction is considered serious (an SAE) if, in the view of the investigator, it results in any of the following outcomes: death, a life-threatening AE, substantial disruption of the ability to conduct normal life functions.

Important medical events that may not meet the above criteria may be considered serious when, based upon appropriate medical judgement, they may jeopardize the subject and may require medical or surgical intervention to prevent one of the outcomes listed in this definition.

Serious adverse events (SAE) will include severe bleeding events (graded as a grade 3 or 4 on the WHO bleeding scale, see Table 1), and treatment-related serious

adverse events, including death, prolongation of existing hospitalization, or a persistent or significant disability/incapacity.

All SAEs will be followed through resolution or stabilization by a licensed study physician. All SAEs will be reviewed and evaluated and sent to the SMC for period review, and the IRB within 7 days of PI-notification, per VUMC IRB policy.

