### **8.3 Reporting of SAE**

Any AE that meets a protocol-defined criterion of an SAE will be reported per local IRB requirements, within 7 days of PI-notification, per VUMC IRB policy.

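### Section 8.1 keeps every condition present at enrollment out of AE reporting with no exception for worsening, so worsening below WHO grade 3 can go uncounted and the handling of grade 3-4 worsening is unclear

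*Protocol*

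**What the plan says.** Section 8.1 defines an adverse event broadly, by its timing relative to the product given ("An AE can therefore be any unfavorable and unintended sign (including an abnormal laboratory finding), symptom, or disease temporally associated with the use of a"), then limits the definition: "Any medical condition present at the time of enrollment will be considered as baseline and not reported as an AE". It narrows collection further, "we are planning to only collect coagulation/hemostasis-related AE's in the study", and adds: "We will use the WHO bleeding scale to grade any bleeding events (table 1").

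Section 8.2 opens the SAE definition with a list of serious consequences ("An AE or suspected adverse reaction is considered serious (an SAE) if, in the view of the investigator, it results in any of the following"), and later states: "Serious adverse events (SAE) will include severe bleeding events (graded as a grade 3 or 4 on the WHO bleeding scale, see Table 1"). It sends all SAEs to the safety monitoring committee (SMC) and the IRB. Section 8.3 words reporting differently: "Any AE that meets a protocol-defined criterion of an SAE will be reported per local IRB requirements".

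Three other places depend on these definitions. Secondary outcome 4 (Section 6.6) is the frequency of bleeding-related adverse events among patients started on prophylactic anticoagulation, by arm. Under Section 8.5 the SMC reviews AE and SAE reports at its six-monthly meetings, and the IRB receives the number of AEs each year. Section 7 describes who would not be considered for anticoagulation: "We would not consider patients for anticoagulation with severe bleeding disorders, clinically significant hemorrhage, severe renal dysfunction", followed by a general clause for anything the investigator judges unsafe.

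**The concern.** AE definitions usually pair a baseline exclusion with an exception for worsening in severity or frequency. Here the exclusion stands alone. Because only coagulation and hemostasis events are collected, the exclusion acts only on the kind of condition that an anticoagulant could aggravate.

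Timing adds to this. Patients are enrolled and randomized on admission, while risk scores are recalculated every day (Section 6.2). Prophylaxis may therefore start some time after baseline is fixed, and a bleed noted on admission remains a baseline condition whatever happens later.

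At stake is the completeness of the trial's bleeding count. Bleeding is a named side effect of the drugs that may be recommended, and bleeding-related AEs are the only safety outcome listed. The trial seeks a waiver of consent on the ground of minimal risk, so the committee and the IRB rely on these counts.

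**Working it through.** No figure in the protocol bears on this point; its one power calculation concerns VTE. The check is to set the rules side by side and follow each course a patient could take.

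| Status at enrollment | Later course | Section 8.1 | Section 8.2 grade 3-4 clause | Result |
|---|---|---|---|---|
| No bleeding, with or without a bleeding disorder | New bleed, any grade | The bleed was not present at enrollment, so it is an AE | Applies if grade 3-4 | Counted |
| Grade 1 bleed | Worsens to grade 2 | Bleed is baseline; not reported | Does not apply | Not counted on a literal reading |
| Hemostasis laboratory abnormality, such as a low platelet count | Worsens without bleeding | Baseline; not reported | Does not apply | Not counted on a literal reading |
| Grade 1 or 2 bleed | Worsens to grade 3 or 4 | Bleed is baseline; not reported as an AE | Lists it as an SAE with no baseline exception | Sections conflict |

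**Rows 2 and 3.** The grade 3-4 clause cannot recover these events, because it does not reach them. The sentence in 8.1 on grading every bleeding event assigns a grade; it does not say that a baseline bleed becomes an AE when the grade rises.

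**Row 4.** Section 8.2 gives a route to SAE status: it names grade 3-4 bleeds directly, also admits a suspected adverse reaction, and forwards all SAEs. Section 8.3 reports an AE that meets an SAE criterion, and 8.1 has said that the baseline condition is not reported as one. No text says which rule prevails.

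**Effect on secondary outcome 4.** Let r be the true rate of bleeding AEs per treated patient in an arm, with worsening counted. Let w be the share of those AEs that are worsened baseline bleeds left out under 8.1. The denominator, patients started on prophylaxis, is unchanged, so

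reported rate = (1 − w) × r.

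The rate is understated in any arm where w is above 0. For the arm comparison, with subscripts I for intervention and C for control,

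reported difference = (1 − w_I) × r_I − (1 − w_C) × r_C.

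If w is the same in both arms, this equals (1 − w) × (r_I − r_C): the difference shrinks towards zero. If w differs between arms, the error can go either way. The protocol gives neither w nor r for either arm, so no number follows.

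**The case against.** The strongest objection is that the gap is narrow. Section 7 keeps patients with clinically significant hemorrhage out of consideration for anticoagulation, and Table 1 attaches that same label to grade 2. Section 7 also leaves room for investigator judgement. Among treated patients, what remains is mainly a grade 1 bleed that reaches grade 2, together with laboratory abnormalities. The broad opening definition in 8.1 might also be read to cover a worsening. The narrowing stands. The broad definition is a weaker answer, because the baseline sentence comes after it in the same paragraph and limits it.

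Three stronger readings are tempting, and the documents support none of them.

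- A reader might infer that a worsened baseline bleed is never counted as an AE or an SAE. Section 8.2 contradicts this for grades 3 and 4: it lists those bleeds without a baseline exception and sends all SAEs to the SMC and the IRB. What remains there is a conflict of wording with 8.1 and 8.3.
- A reader might assume a prevalence of baseline conditions and a relative bleeding rate, and so derive a percentage of lost events. The protocol gives neither input. Such a sum would also treat every bleed in a child with a baseline condition as excluded, although 8.1 does not exclude a new bleed in a child with a mild bleeding disorder.
- A reader might infer that the loss falls mainly on the intervention arm and hides excess harm, since control patients are rarely offered prophylaxis. Secondary outcome 4 divides by treated patients within each arm, so more treatment in one arm does not by itself make the loss differential.

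The SMC's access to outcome data does not close the gap as far as bleeding is concerned, because secondary outcome 4 is itself built on adverse events.

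**Conclusion.** The point holds in a limited form. Section 8.1 fixes a categorical baseline rule with no provision for worsening. Followed as written, it leaves sub-grade-3 worsening of a bleed or other hemostasis abnormality present at enrollment out of AE reporting. Worsened bleeds of this kind can then be missing from secondary outcome 4, and all such events from the AE counts that go to the SMC and the IRB. For worsening to grade 3 or 4, the protocol does not settle how 8.1 and 8.3 fit with 8.2.

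The direction for each arm's reported bleeding rate is downward, if any such events occur. The size, and the effect on the arm comparison, cannot be determined from the protocol. The conclusion assumes that staff apply 8.1 literally; staff who treat worsening as a new event would already count it, but the text does not tell them to. It is worth amending because the rule is part of the protocol's own AE definition and the correction is small.

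**What to change.** Amend the baseline sentence in Section 8.1 along these lines: *A condition present at enrollment is baseline and is not an AE unless it worsens after randomization. For bleeding, any increase in WHO grade above the grade at enrollment is an AE. This applies equally in both arms.* Then add to Section 8.2, with a cross-reference in 8.3: *A grade 3 or 4 bleed is an SAE and is reported as such whether or not bleeding was present at enrollment.*

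This changes only what is counted and reported, not how any patient is managed. It takes a short protocol amendment. The enrollment grade has to be read from the chart, but only for patients who bleed, and the reported bleeding rate may rise slightly.

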### 8.2 Definition of Serious Adverse Event

An AE or suspected adverse reaction is considered serious (an SAE) if, in the view of the investigator, it results in any of the following outcomes: death, a life-threatening AE, substantial disruption of the ability to conduct normal life functions.

Important medical events that may not meet the above criteria may be considered serious when, based upon appropriate medical judgement, they may jeopardize the subject and may require medical or surgical intervention to prevent one of the outcomes listed in this definition.

Serious adverse events (SAE) will include severe bleeding events (graded as a grade 3 or 4 on the WHO bleeding scale, see Table 1), and treatment-related serious

adverse events, including death, prolongation of existing hospitalization, or a persistent or significant disability/incapacity.

All SAEs will be followed through resolution or stabilization by a licensed study physician. All SAEs will be reviewed and evaluated and sent to the SMC for period review, and the IRB within 7 days of PI-notification, per VUMC IRB policy.

### **8.3 Reporting of SAE**

Any AE that meets a protocol-defined criterion of an SAE will be reported per local IRB requirements, within 7 days of PI-notification, per VUMC IRB policy.

### **8.4 Recording of AEs/SAEs**

Information regarding AEs and SAEs will be collected will be uploaded into a password-protected computerized database maintained within a secure, web-based application for building and managing online databases (REDCap) [see section 10].

### **8.5 Safety Monitoring Committee**

Although the study poses no greater than minimal risk to participants, a safety monitoring committee (SMC) will be appointed to ensure the continuing safety of research participants, appropriateness of the study and to monitor termination criteria. The SMC will be comprised of three individuals with expertise relevant to the study, including pediatric medicine, biostatistics, and prior experience serving in this capacity. The SMC will be independent of the study team and will meet every six months. During these meetings, the SMC will review adherence to the protocol, reports of SAE and AE. The SMC will not perform any interim analyses but will be provided outcome data to inform safety decisions. The SMC will make recommendations regarding whether the study should continue unchanged or require modification/amendment. Based on the findings of the SMC reports, the study team may also elect to halt, suspend, or modify study.

The PI will be responsible for overseeing the study. They will be available at any time for questions from clinically relevant providers. They will also record adverse events and serious adverse events. Study-related SAE will be recorded in the study record and reported to the IRB within 7 calendar days of PI-notification. Summary reports will be submitted to the IRB annually and will contain a) the number of adverse events and b) the number of protocol violations and how each was handled.

## 9 Study Withdrawal/Discontinuation

Due to the study design, withdrawals are not anticipated. The primary focus of our study is to determine if a the EHR-based VTE risk prediction tool increases the number of high-risk patients reviewed by the VTE research team. Patients in both arms will continue to receive the current standard of care clinical practice for inpatient prophylactic anticoagulation. High-risk patients in the intervention arm will receive an additional chart review and subspecialty expertise.

## 10 Statistical Considerations

### 10.1 Statistical Analysis Plan

Primary analyses will be conducted at the encounter level, while secondary analyses will be conducted at the patient level (patients can potentially experience multiple encounters during the study period).

The rate of VTE events (primary outcome), the proportion of patients receiving prophylactic anticoagulation (secondary outcome), and the rate of bleeding-related adverse events (secondary outcome) will be compared between the intervention and control arms using unadjusted risk differences with 95% confidence intervals. We have not specified *a priori* any adjustment variables to include in multivariable models. Any variable with a clinically meaningful imbalance between the intervention and control groups will be adjusted for in multivariable regression models; given the large sample size we do not anticipate any such imbalances. For the primary outcome, a two-sided p-value (obtained from Pearson's chi-square test) of  $< 0.05$  will indicate statistical significance. Secondary subgroup analyses will be performed by patient gender, risk of VTE, primary diagnoses, surgical vs. nonsurgical, and consultants involved.

Primary analyses will be conducted by intention-to-treat; secondary analyses will be as treated, considering whether treatment recommendations were followed by the admitting team. Secondary as-treated analyses will be performed among the strata of high-risk patients (predicted probability  $\geq 0.025$ ) randomized to usual care, to the intervention but treatment recommendations were not followed, and to the intervention and treatment recommendations were followed.

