## 4 Eligibility Criteria

Inclusion criteria:

1. All pediatric patients 0-21 years of age who are admitted to an inpatient unit of Vanderbilt Children's Hospital (VCH) will be included in the study.

Subjects must not meet any of the following exclusion criteria:

1. Receiving prophylactic or therapeutic dosing of anticoagulants, including enoxaparin, warfarin, bivalirudin, apixaban, rivaroxaban, dabigatran, and edoxaban.
2. Patients admitted under "observation status"

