### **5.2 Randomization**

Patients will be randomized 1:1 to the intervention or control arms upon admission via an automatic process built into the electronic health record. Both arms will continue to receive local standard of care practice for VTE prophylaxis.

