### **6.4 Outcomes**

### **6.5 Primary Outcomes**

The primary outcome will be to determine whether the number of VTE events is lower in the intervention arm than the control arm. The endpoint measure will be calculated as the frequency of VTE events per hospital admission encounter per arm.

VTE outcomes will be tracked in both arms of the study on a monthly basis. The radiology coordinator will provide a report of all pediatric radiology studies completed in the prior month. The VTE research team will filter the data based on the location that the imaging was performed (such as inpatient at VCH) and type of radiology study to best identify VTEs (such as ultrasounds with doppler and CT-angiograms). We will then review the filtered report to identify the MRN of patients and the date of the VTEs that were identified during that time period.

An additional data sample will be obtained from the EMR one month after enrollment completion to assess ICD9/ICD10 codes for acute VTE (utilizing codes established during model development and validation) during the trial period to further confirm all VTE events were appropriately captured in the monthly reports.

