### 10.2 Sample Size Considerations

At least 15,000 patients (~1 year of data), and no more than 45,000 patients (~3 years of data), will be randomized 1:1 to the intervention or control arms. If we assume an overall median risk of 1%, we will achieve 80% power to detect a risk reduction from

1% to 0.595% if there are at least 7500 subjects per group. We are aware that due to the low baseline event rate, we may need to enroll additional patients to achieve the necessary power. This will be the largest randomized controlled trial ever performed to answer this important question in pediatrics and will therefore be an important contribution to the literature both for pediatric hematology and in the field of pediatrics.

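### Protocol 5.2 does not say whether a readmitted child keeps the arm, so the encounter-level chi-square and the patient-level by-arm analyses in 10.1 cannot both stand as written

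*Protocol*

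**What the plan says.** - **Allocation (Protocol 5.2).** "Patients will be randomized 1:1 to the intervention or control arms upon admission via an automatic process built into the electronic health record". Nothing follows about a child who is admitted again.
- **Primary endpoint (6.5).** It is the "frequency of VTE events per hospital admission encounter per arm".
- **Analysis units (10.1).** "Primary analyses will be conducted at the encounter level, while secondary analyses will be conducted at the patient level". The same sentence adds that "patients can potentially experience multiple encounters during the study period".
- **Primary test (10.1).** An unadjusted risk difference with a 95% confidence interval, and "a two-sided p-value (obtained from Pearson's chi-square test"), judged at 0.05.
- **Secondary outcomes (6.6).** The first two count patients started on prophylaxis in each study arm, so each patient needs one arm.
- **Sample size (10.2).** 15,000 to 45,000 patients, with 80% power for 1% versus 0.595% "if there are at least 7500 subjects per group". There is no allowance for repeat encounters.
- **Eligibility (4).** A child is excluded if "Receiving prophylactic or therapeutic dosing of anticoagulants".

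The protocol does not mention persistence of the arm, clustering, robust variance or a first-encounter restriction.

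**The concern.** The protocol fixes the unit of analysis and the test itself, and it recognises recurrence without dealing with it. This is therefore more than a detail left to a later plan. Two designs fit the text, and each has a different fault.

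1. **The child keeps the arm.** That child's encounters share both arm and underlying risk. Pearson's chi-square and the unadjusted interval treat them as independent rows, so the standard error is too small when the correlation is positive.
2. **Every admission is randomized afresh.** The primary analysis then matches the unit of randomization. However, one child can appear in both arms, and the patient-level comparisons do not say where that child counts. An earlier event or recommendation can also affect care in a later control encounter: section 6.3 says that prophylaxis in usual care is largely confined to children with a known previous VTE.

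At stake are the error rate and interval of the only formal test under the first design, and the definition of the by-arm secondary outcomes under the second.

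**Working it through.** **1. The plan's own power.** Inputs from 10.2 and 10.1: p1 = 0.01, p2 = 0.00595, n = 7500 per arm, two-sided alpha 0.05. The usual two-proportion formula without continuity correction gives power 79.6%; exactly 80% needs 7571 per arm. The stated figure reproduces, but the formula assumes 7500 independent observations per arm.

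**2. What N counts.** Section 2.2 reports 111,352 admissions from 1/1/2010 to 10/31/2017, which is 7.83 years: 111,352 / 7.83 ≈ 14,200 admissions a year. Section 10.2 equates 15,000 patients with about one year. The planned N therefore looks like a count of admissions labelled as patients.

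**3. If the arm persists.** With m encounters per patient and size-weighted mean k = E[m²]/E[m]:

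- design effect DE = 1 + ICC × (k − 1)
- true type I error = 2 × [1 − Φ(1.96/√DE)]
- power is evaluated at 7500/DE per arm, and the n needed is 7571 × DE

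The protocol gives neither ICC nor k, so both are assumptions. One figure gives a rough guide to the ICC: history of thrombosis has an odds ratio of 8.7 (2.2). Under exchangeable correlation, ICC = (q − p)/(1 − p), where q is the risk given a previous event.

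- p = 815/111,352 = 0.73%: odds 0.00737 × 8.7 = 0.0641, q = 6.0%, ICC ≈ 0.05
- p = 1%: odds 0.0101 × 8.7 = 0.0879, q = 8.1%, ICC ≈ 0.07

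| ICC | k | DE | Type I error | Power | n per arm for 80% |
|---|---|---|---|---|---|
| 0.02 | 2 | 1.02 | 5.2% | 79% | about 7,720 |
| 0.05 | 3 | 1.10 | 6.2% | 76% | about 8,330 |
| 0.07 | 4 | 1.21 | 7.5% | 72% | about 9,160 |

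A simulation checked the formula (beta-binomial events, about 15,000 encounters, skewed numbers of admissions, 1500 runs per scenario, simulation standard error about 0.6 percentage points). With a mean of 1.5 encounters per patient, k is 2.39. At ICC 0.10 the formula gives 6.6% and the simulation 6.1%. At ICC 0.20 they give 8.3% and 8.1%.

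**4. If each admission is re-randomized.** The simulated chi-square error stayed near nominal (3.7% to 5.6% across scenarios). About 8% of patients (mean 1.2 encounters) to 17% (mean 1.5) had encounters in both arms. These shares depend on the assumed distribution of admissions.

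**5. Re-entry.** Section 4 excludes children on anticoagulants. If arms persist and the intervention changes how many children are anticoagulated at readmission, later encounters could be selected differently by arm. If each admission is re-randomized, eligibility comes before the new allocation and cannot depend on it.

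**The case against.** The strongest reply is that the trial randomizes admissions, so the primary test is sound. Enrolment and allocation occur at admission (5.2, 6.1), each participant's study runs to discharge or death (12), the endpoint is per encounter (6.5), and N per year matches admissions (10.2 against 2.2). This is a plausible reading, and under it the chi-square roughly keeps its size. It does not settle the matter, because 5.2 and 10.2 speak of patients and the patient-level arm would still be undefined.

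A reader might infer three stronger things that the documents do not support.

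- **That the primary analysis is invalid whichever unit is meant.** It is not: under re-randomization the fault moves to the secondary analyses and to carry-over.
- **That type I error reaches about 12%.** That needs an ICC of 0.20 with k = 4 (DE 1.60). The odds ratio of 8.7 points to about 0.05 to 0.07. It is an imperfect guide: it may be adjusted for other variables, and other stable risk factors could add correlation. In the other direction, excluding anticoagulated children at readmission removes some of the repeat events that would create correlation.
- **That later encounters are certainly selected by arm.** This is possible only if the arm persists. The protocol does not describe discharge on prophylaxis, and section 12 ends the study intervention at discharge.

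**Conclusion.** The point holds as an unresolved ambiguity with a definite consequence on each side. The protocol does not say whether the arm persists across readmissions, and its sample size carries a patient label on what looks like an admission count.

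If the arm persists, the primary p-value and interval are likely too narrow. Under the assumed ICC of 0.02 to 0.07 and k of 2 to 4, type I error is about 5.2% to 7.5% rather than 5%, and power about 79% to 72%. The inflation is negligible at the low end and larger only if correlation or recurrence exceeds these assumptions. The power arithmetic is correct for independent observations.

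If each admission is re-randomized, the primary test is approximately valid. The patient-level by-arm comparisons then lack a rule for children seen in both arms, and carry-over into later encounters remains possible.

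The documents do not show that the primary result would be wrong, nor that one randomization per patient is the required design. Either design can work once it is stated and the analysis matched to it.

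**What to change.** 1. **Section 5.2:** state whether a readmitted patient keeps the first arm or is randomized again. This should describe how the health-record system actually allocates.
2. **Section 10.1, primary analysis:** replace the plain chi-square and its interval with the encounter-level risk difference using patient-clustered robust standard errors (GEE, independence working correlation). This gives a valid standard error under either reading.
3. **Section 10.1, sensitivity analysis:** pre-specify an analysis of the first eligible encounter only. It has one row per patient, so the chi-square is valid and neither re-entry selection nor carry-over from an earlier trial encounter can act.
4. **Section 10.1, patient-level analyses:** run them by the first assigned arm. If admissions are re-randomized, note that later encounters in the other arm may dilute the contrast.
5. **Section 10.2:** express N in the unit analysed. If the arm persists, add a design effect with its assumed recurrence and correlation.

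The cost is a little more analysis work and a slightly wider interval: the width grows by √DE, about 1% at DE 1.02 and 10% at DE 1.21. No change to the randomization itself is needed.
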